## Abstract

Self-determination is regarded as an adult outcome for people with an intellectual disability (ID). However, self-determination curricula are rarely available in Hong Kong. This paper outlines a protocol for an experimental study that examines the effectiveness of a group-based self-determination enhancement intervention for adults with mild ID and their caregivers. A randomized controlled trial with pre-test, post-test and three-month follow-up is proposed. A total of 120 participants will be randomly assigned to three conditions: self-determination enhancement group, self-determination enhancement PLUS group (with caregivers in a parallel group) and leisure activity group as a control condition. Five groups will be organized for each of the three conditions. There will be 10 sessions per group covering the core components of self-determination including self-knowledge, goal setting and attaining goals, self-regulating and adjusting plans. Components for caregivers include understanding how self-determination and REACH responding skills can support their children to exercise self-determination through positive interaction. Self-determination competencies and personal well-being will be measured at three points in time. The proposed study is the first evidence-based local study aimed at examining a culturally tailored self-determination enhancement intervention for people with ID and fills a research gap in existing interventions. If the intervention is demonstrated to be effective, it will provide new knowledge for a group-based intervention and will be used with Chinese-speaking people with ID in different parts of the world. (Trial registration: ClinicalTrials.gov: NCT05167929)

## 1. Introduction

Personal self-determination was recognized as a human right by the United Nations (UN) in 1967 [1], and Nirje [2] asserts that people with disabilities should be accorded the same right to self-determination as everyone else. The UN Convention on the Rights of People with Disabilities and the World Health Organization have stressed the importance of self-determination (including choice-making, decision-making and participation) for people with disabilities’ dignity and mental health; self-determination is also a key feature and corresponding criterion for the delivery of quality in social services [3,4]. Since the late 1990s, the concept of self-determination has developed significantly in the international field of intellectual disabilities (ID). Many studies have evidenced the importance of self-determination in different areas of the lives of people with ID. Firstly, people with ID who have higher levels of self-determination attain better academic performance [5] and achieve more positive adult outcomes including the following: autonomous community living [6,7]; more independence, being more financially independent or obtaining better job benefits [8,9]; and higher quality of life [10], such as higher life satisfaction, better personal well-being and attaining more meaningful engagement with others [9,11,12,13,14,15]. Self-determination competencies also positively correlate with personal well-being for people with ID in Chinese societies [16], confirming that self-determination is cross-culturally important to people with ID.

Scholars have stated that self-determination is a multifaceted construct [17]. Self-determination theory (SDT) [18,19,20] suggests that self-determination is the capacity to choose and proposes that autonomy, relatedness and competence are three universal and intrinsic human needs that motivate people to become involved in activities [18,21,22]. Autonomy refers to people initiating actions for themselves, from their integrated values and interests and feeling ownership over their actions [19]. The activities might be in accordance with the person’s own thoughts or might be influenced by others [23]. Relatedness refers to a sense of belonging and connection with others; that a person cares for and is cared for by others [19,23,24]. Competence refers to a sense of mastery [19], and a felt sense of confidence [23]. A person experiences satisfaction through overcoming optimal challenges, expressing his or her talents and capacities and feeling able to succeed and grow [19,23]. The functional theory of self-determination suggests that a self-determined person possesses specific capacities (behavioral autonomy and self-regulation) and attitudes (psychological empowerment and self-realization) that coexist in the consistent performance of self-determined actions. The theory also proposes 12 component elements of self-determined behavior (concerning choice-making skills, goal-setting and goal-attainment skills, self-knowledge skills, etc.) [25,26,27]. The theory stresses that one’s capacity for self-determination can be enhanced through learning and can be developed when opportunities to do so are available in one’s environment. The ecological theory of self-determination suggests that self-determination occurs as a result of the ongoing interplay between individuals and multiple environments [28]. An individual is at the center of multiple systems, and his or her self-determination competencies (i.e., attitudes, knowledge and skills) influence how he or she interacts with the external environment with regard to issues of self-determination [29]. The self-determined learning theory stresses that self-determined people are effective regulators in the goal pursuit process; they will try to adjust their expectations or explore more favorable environmental conditions when there is a discrepancy between their existing state and their desired goal [30,31]. Individuals are often in flux between their existing states and personal goals. In the course of the fluidity process, more self-determined people will try to set appropriate expectations when matching their competency (the assessment of their own existing skills, interests and motivations) with the present opportunity; they will take into consideration their own strengths and constraints as well as environmental factors (both human and situational factors) and then make adjustments whenever necessary [32]. The self-determination process involves various elements including self-understanding, personal preferences, goal setting, plan setting, choice making, decision making, problem solving, self-management, plan reviewing and self-regulation. This theory proposes that, to become a more self-determined person, an individual needs to learn to make adjustments when necessary at different stages in the self-determination process.

A social-ecological perspective proposes that family, as a microsystem, plays a crucial role in influencing an individual’s self-determination [33,34]. Studies have shown that the parents of students with ID tend to recognize the importance of self-determination skills; however, they do not engage their children extensively in exercising these skills at home [35]; although parents try helping their children to exercise self-determination skills at home, their approaches differ from what their children learn at school [36,37]. Cultural factors are also regarded as a vital consideration in a person’s development and practice of self-determination [33,38]. The development of self-determination, opportunities to promote it and supporting elements that enable its expression are affected by multiple cultural factors such as race and ethnicity, gender, disability status, socioeconomic status and language [33]. For example, parents from Western cultures pay more attention to independence than those from non-Western cultures [39]. In Chinese collectivist culture, people may be more comfortable with demonstrating their self-determination competencies than their self-determination autonomy [32]. While recent studies conducted in Western countries have begun to stress autonomy support and partnership in decision-making from paid and unpaid caregivers [40,41,42], people with ID in Chinese societies have less autonomy in financial matters and over major life decisions [43].

The literature shows that the effectiveness of self-determination curricula and interventions in enhancing general self-determination skills has been demonstrated. The core components of self-determination curricula and interventions in Western countries mainly comprise self-knowledge, goal-setting and planning skills, choice- and decision-making skills, problem-solving skills, self-advocacy and management skills and self-evaluation and outcome expectation skills. However, these classroom-based self-determination curricula and interventions mainly focus on schooling or transitional periods; while self-determination is relevant across the life span, there is very little curriculum focus on adults [44]. In addition, the majority of self-determination curricula or intervention packages have been developed for students with diverse kinds of disabilities in the school context or at the point of transition to adulthood [31,45,46]. Although the literature has mentioned the importance of working on parents’ values, beliefs and perceptions regarding their children’s potential for self-determination [47] and has identified an ongoing need to provide parents with opportunities to learn about self-determination and how to facilitate their children to exercise it [48], very few studies provide training for parents of people with ID. In recent years, self-determination theory has been applied in diverse fields such as parenting and education, as well as in regard to life goals [49]. Studies in the general population have evidenced the effectiveness of need-supportive [50] and autonomy-supportive practices [51,52] conducted by teachers and parents to enhance children’s and adolescents’ motivation to engage in learning activities and reduce academic stress. Need-supportive practices emphasize taking others’ perspectives and trying to tune in to others’ psychological needs for competence, autonomy and relatedness, as well as demonstrating empathetic responses [50]. Autonomy-supportive practices suggest adopting autonomy-supportive behaviors (e.g., avoiding controlling behavior and language and adopting children’s perspectives) and providing structure (i.e., setting clear goals, expectations and directions) to enable individuals to sustain their perception of competence [51]. These practices also encourage the provision of rationales that foster the internalization of individuals’ motivations [52]. In Hong Kong, there is no well-developed curriculum tailor-made for people with ID, particularly for adults with ID [16]. Therefore, considering the importance of caregivers in self-determination and the cultural characteristics of Chinese societies, the author proposes a group-based, culturally tailored intervention for enhancing self-determination among adults with mild intellectual disability and their caregivers.

### 1.1. Conceptual Framework of the Intervention and Its Delivery Approach

Studies have recognized that self-determination competencies such as goal setting, planning, choice making and self-regulation are applicable to Chinese people [32,53]. In this regard, the proposed intervention adopts key learning elements from Western self-determination curricula, e.g., [30,46,54], developing a six-stage process of goal pursuit: (1) knowing myself, (2) setting a personal goal, (3) planning for achieving the goal, (4) acting to attain personal goals, (5) reviewing and regulating the goal/plan and (6) personal goal is attained. In stage five, ‘reviewing and regulating the goal/plan’, when there is a need to regulate the goal or the plan, the learners will be facilitated to go back to stage two, ‘setting a personal goal’ or stage three, ‘planning for achieving the goal’ to adjust the goal or the plan accordingly (see Figure 1).

Studies conducted in Hong Kong suggest that family members, particularly parents, play an important role in the exercise of self-determination by people with ID. There is a process of searching for equilibrium in working towards self-determination, in which adults with ID simultaneously consider the views of their parents and concern their feelings when making decisions, while parents struggle between autonomy support and protectiveness, trying to strike a balance in different situations [16,43]. Taking this culturally specific dimension into account, this study’s intervention develops and incorporates the state called self-determination fit at stages four and five; this encourages adults with ID to find the state of self-determination fit during the process of searching for equilibrium (see Figure 1). In the process of acting on the plan, people with ID maintain an ongoing review of themselves and on their situation. When necessary, they should be assertive in creating opportunities for themselves (e.g., seeking support or tangible help from caregivers or others). However, if after recognizing intractable constraints and/or considering caregivers’ or others’ views, they find the plan or the goal is unrealistic, they may then understand that they need to regulate the plan or goal. The process of identifying the state of self-determination fit helps people with ID to clear their minds and recognize their own ways of regulating the plan or goal accordingly.

To enhance caregivers’ autonomy support, based on the aforementioned intrinsic psychological needs and autonomy-supportive practices, this study develops a set of responding skills called REACH (i.e., rationale giving, empathy showing, acting out, companion and highly praising). Providing a rationale using noncontrolling language leads to autonomous motivation [55,56,57,58]. In this intervention, we encourage caregivers to explicitly express a rationale or reasons to the participants, regardless of whether or not they support their children in pursuing the plans (*rationale giving*). Caregivers are also encouraged to show empathy, because the participants may experience ups and downs and may sometimes feel excited and sometimes upset in the course of goal pursuit (*empathy showing*). Besides being psychologically connected, walking together (*companion*) with the participants along the journey of goal pursuit (e.g., rendering practical help or accompanying them to particular activities) is also important as giving these tangible assistance makes things easier than if the participants faced the challenges alone. *Highly praising* includes giving positive feedback and showing the participants recognition and appreciation. These modes of support have the potential to help people with ID become more competent [19] and facilitate them to have more energy and power in pursuing their personal goals. *Acting out* means encouraging caregivers to act out all the above four skills explicitly to show they support the participants in their journey toward goal pursuit.

We propose adopting a group-based mode of delivery for the intervention; the target groups are adults with mild ID and their caregivers. While most empirical self-determination training in Western countries is designed for students and is based on classroom curricula, this study proposes groupwork as the intervention method for adult participants with ID. The advantages of group-based intervention such as modelling, role playing, reciprocal learning, peer support, group problem solving, individual change caused by group dynamics and interpersonal change processes are proven and well-recorded methods [59,60,61]. Therefore, firstly, the groupwork learning environment provides effective moments for participants with ID to learn subjects relating to interactional person-in-environment situations, such as the process of self-determination fit. Secondly, groupwork is more effective than one-way lecturing in helping adult participants integrate the self-determination skills learned in the group into real-life situations. This intervention emphasizes the importance of adults with ID practicing the goal pursuit steps in real-life situations, in accordance with their own individual goals and plans. The participants with ID are thus required to try out their own plans during the intervention (group sessions 6 to 9). Some of their caregivers will be involved in a dyadic intervention, learning what self-determination is and practicing the REACH responding skills to support the participants in their goal pursuit.

The instructional strategies for the intervention recognize that the elements of working memory, a main component of executive function, and emotion regulation have been shown to facilitate people with ID in acquiring skills [62]. In our curriculum, we will employ slogans as well as visual cues such as diagrams, flow charts and videos during training. We anticipate that, through improving their working memory, participants with ID can learn self-determination skills and apply them in their daily lives more easily.

### 1.2. Study Objectives

The objectives of the study are to develop a group-based, culturally tailored self-determination enhancement intervention for adults with ID and to examine its effectiveness.

## 2. Materials and Methods

### 2.1. Study Design, Aims and Hypotheses

This study is a randomized controlled trial (RCT), where adult participants with mild ID and their caregivers are randomized into three arms: (1) self-determination enhancement group (SD group), (2) self-determination enhancement PLUS group (SD-PLUS group) and (3) leisure activity group (comparison group, hereafter called leisure group). SD-PLUS is the only group to include caregivers during the intervention. There will be three assessment points: pre-test (T0), post-test (T1) and follow-up (3 months later) (T2); see Figure 2 for a diagrammatic representation of the study’s design structure. To ensure equity of access to a potentially effective intervention, participants in the leisure group will receive the same SD group intervention following completion of all the assessments for the intervention arm. The study protocol was approved by The Survey and Behavioral Research Ethics Committee of The Chinese University of Hong Kong (reference no.: SBRE-18-234) and the trial was registered in the ClinicalTrials.gov Protocol Registration (registration no.: NCT05167929).

This study aims to evaluate the effectiveness of the intervention. There are three intervention conditions: (1) SD group—only attended by participants with ID; (2) SD-PLUS group—in the form of a parallel group structure, in which the participants’ caregivers will attend the caregivers’ group; and (3) leisure group—only attended by participants with ID. The hypotheses for the study are as follows:(1)Participants in the SD group and the SD-PLUS group, in comparison with participants in the leisure group, will enhance their self-determination competencies and personal well-being during the post-intervention phase (T1);(2)Participants in the SD group and the SD-PLUS group, in comparison with participants in the leisure group, will enhance their self-determination competencies and personal well-being at the three-month follow-up (T2);(3)Participants in the SD-PLUS group, in comparison with participants in the SD group, will exhibit additional enhancements in their self-determination competencies and personal well-being during the post-intervention phase (T1);(4)Participants in the SD-PLUS group, in comparison with participants in the SD group, will exhibit additional enhancements in their self-determination competencies and personal well-being at the three-month follow-up (T2);(5)Parent participants in the SD-PLUS group will enhance their beliefs, perceptions and skills in regard to supporting their children in exercising self-determination during the post-intervention phase (T1) and at the three-month follow-up (T2).

It will be a challenge for participants recruitment if three intervention conditions are required. However, since this kind of program has never been tried and tested in Hong Kong, the grant’s vetting reviewers suggested to test the program with three conditions.

### 2.2. Ethical Concerns

Written consent will be sought both from the adult participants with mild ID and their caregivers. People with ID should be accorded as much respect as any other members of the population in terms of their having the autonomy to decide whether or not to participate in research [63]. In addition, this study is concerned with self-determination, and therefore the process of participation is itself a manifestation of self-determination for the participants. Additional measures suggested by the International Handbook of Applied Research in Intellectual Disabilities [64] will be adopted as follows: (1) An individual consent session will be arranged for every potential participant. The content of the consent form will be presented to the participants using plain language and incorporating pictures as visual cues. The participants will then be asked to sign the consent form. (2) A passive consent form will also be used to give dual protection to participants’ rights. Once the participants have signed the consent form, they will then be asked to give consent to us to contact their parents or guardians. Passive consent will then be sought from the parents or guardians.

### 2.3. Sample Size

The sample size is calculated based on a moderate effect size of 0.70 for clinical outcome research. For 80% power, an α error of 0.05, and a test including three independent groups, the required sample size is 105 participants, which is sufficient to conduct Hierarchical Linear Modelling (HLM). Incorporating an estimated drop-out rate of 15% at the six-month follow-up period, the target sample size is 120. Drop-out cases will include participants with ID whose attendance rate in regard to the groups is less than 70%, or those who cannot complete all questionnaires during the three phases. With 6–8 participants per group, 5 SD groups, 5 SD-PLUS groups and 5 leisure groups will be conducted.

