### 2.12. Statistical Analysis

Analyses of the outcomes will be performed using the intention-to-treat principle; this method is used to avoid the effects of crossover and drop-out in clinical research. Parameters for those who withdraw will be treated using maximum likelihood estimation (i.e., the full information maximum likelihood method). This method produces approximately unbiased results across a variety of parameter estimates, particularly with a small sample size [69]. Prior to all hypotheses testing, this study will conduct a Chi-square test and a *t* test to assess whether or not the sociodemographic characteristics and the baseline conditions of the participants with ID are different among the groups. Analyses of treatment outcomes will be conducted using hierarchical linear modelling (HLM), which is suggested to have more flexible data requirements (dealing with the missing data), and stresses individual change over group differences. Moreover, the HLM analysis is able to identify differences between conditions through the presence of a significant time x treatment interaction term. To examine the magnitude of change in the three groups at post-test and follow-up, effect size statistics will be calculated using Cohen’s d [70]. Finally, regression analyses will be performed to examine the relationships between changes in self-determination competencies and personal well-being among the participants with ID.

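### The drop-out allowance is computed the wrong way: 105 evaluable with 15% loss needs 124, while 120 leaves 102 and already fills all 15 groups

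*Protocol article*

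**What the plan says.** All the figures stand in section 2.3 (Sample Size) of the protocol article.

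- Effect size: "The sample size is calculated based on a moderate effect size of 0.70 for clinical outcome research".
- Requirement: "For 80% power, an α error of 0.05, and a test including three independent groups, the required sample size is 105 participants".
- Allowance for loss: "Incorporating an estimated drop-out rate of 15% at the six-month follow-up period, the target sample size is 120".
- Delivery: "With 6–8 participants per group, 5 SD groups, 5 SD-PLUS groups and 5 leisure groups will be conducted".

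The same section defines drop-out broadly: it covers participants who attend less than 70% of sessions and those who do not complete the questionnaires at all three time points. The Abstract repeats the total: "A total of 120 participants will be randomly assigned to three conditions". Section 2.12 plans an intention-to-treat analysis by hierarchical linear modelling, with full-information maximum likelihood for those who withdraw, and says that "effect size statistics will be calculated using Cohen’s d".

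**The concern.** Three figures in one paragraph (105 required, 15% lost, 120 enrolled) should follow from one another, and they do not. If the stated loss occurs, the trial ends below the number that the section itself calls required. The allowance looks like 15% but protects against less.

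The delivery plan then leaves no room to put this right. The enrolment target equals the maximum capacity of the planned groups, while the same sentence permits groups of six. Section 2.1 says that recruiting for three conditions will be a challenge, and section 2.4.2 says that incentives cannot be offered, so groups of fewer than eight are a realistic prospect. This paragraph is the article's only justification of power, and a reader cannot see from it what happens to the 80% when groups are not full.

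**Working it through.** **Inputs from section 2.3:** effect size 0.70, power 80%, α = 0.05, three groups, requirement 105, loss 15%, target 120, 5 + 5 + 5 = 15 groups of 6–8.

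**Assumptions:** 0.70 is read as Cohen's d, the metric named in section 2.12; the test is two-sided; the arms are equal (five groups each); clustering within groups and multiplicity are ignored.

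**1. The requirement of 105.** For a two-sample t-test with n per arm, df = 2n − 2, the noncentrality is d·√(n/2), and power is the probability that |T| exceeds the 97.5% point of t.

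| n per arm | noncentrality | power at d = 0.70 |
|---|---|---|
| 33 | 0.70 × √16.5 = 2.84 | 79.97% |
| 34 | 0.70 × √17 = 2.89 | 81.2% |
| 35 | 0.70 × √17.5 = 2.93 | 82.3% |

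The smallest n reaching 80% is 34, so three arms need 3 × 34 = 102. The stated 105 is 35 per arm, three above this, and is sufficient for such a comparison.

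As a cross-check, take a three-group F-test with 0.70 between the extreme arms. It needs 123 if the third mean lies midway (f = 0.70 × √(1/6) = 0.286), and 93 if it coincides with one extreme (f = 0.70 × √2/3 = 0.33). The figure 105 lies between these two.

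**2. The allowance for loss.**

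- Correct inflation: 105/(1 − 0.15) = 123.5, so 124. Equal arms would need 42 each, or 126.
- Shortcut: 105 × 1.15 = 120.75. Rounded down, this is the stated 120.
- Retained from 120: 120 × 0.85 = 102, or 34 per arm, three below 105.
- Loss at which 120 still leaves 105: 1 − 105/120 = 12.5%.
- Starting from 102 instead: 102/0.85 = 120 exactly. The sequence 102 → 120 → 15 groups of 8 is therefore consistent; the sequence that starts at 105 is not.

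**3. Capacity.**

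- 15 × 6 = 90 and 15 × 8 = 120, so 120 is reached only with eight in every group.
- 124/15 = 8.27 per group, above the stated maximum.

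**4. Power under the stated loss (pairwise t-test, d = 0.70, before clustering).**

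| Enrolled | Retained after 15% loss | Per arm | Power |
|---|---|---|---|
| 120 (all groups at 8) | 102 | 34 | 81% |
| 90 (all groups at 6) | 76.5 | about 25 | 68% |

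With the unrounded 25.5 per arm, the second row gives 69%.

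**The case against.** The strongest reply is that the slip changes almost nothing. It costs three people, one per arm, and 34 per arm still gives 81% for a pairwise comparison at d = 0.70, so the stated 80% survives. Section 2.12 also keeps withdrawn participants in the analysis through maximum likelihood, which makes 102 a cautious count of the information available. Both points stand, and they make this a minor matter. They do not make 120 the right answer to 105 with 15% loss.

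It may also be said that 90 enrolled is a worst case that the protocol nowhere plans, and that a t-test at one time point is not the planned three-wave model. Both are true. The 68% marks the lower end of the permitted group size and is not a forecast; all the power figures here are guides.

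Several stronger readings are tempting, but the document does not support them:

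- *That 105 cannot be reproduced.* It is close to three arms of a pairwise t-test (102) and lies between the two F-test answers (93 and 123). The test is not named, but a condensed article may leave that to the full protocol or analysis plan.
- *That 90–120 contradicts 120.* The range contains the target. What can be said is that there is no slack.
- *That the six-month wording conflicts with the three-month follow-up.* Section 2.1 lists "pre-test (T0), post-test (T1) and follow-up (3 months later) (T2". The sessions span about ten weeks (section 2.9.1) and T2 comes three months after completion (section 2.7), so T0 to T2 is roughly six months. The phrase can mean that whole span.
- *That calling 0.70 moderate is an error.* This rests on a convention outside the document, and it alters no number.
- *That the comparison of SD-PLUS with SD is shown to be underpowered.* Section 2.3 does not say that 0.70 applies to that comparison, and any smaller effect would be an assumption of the reader.

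**Conclusion.** The point holds for the drop-out step. On the section's own numbers, with no outside assumption, 120 is too few to retain 105 after a 15% loss: 124 are needed, 102 would remain, and 120 covers only 12.5%. It also holds that 120 is the ceiling of the planned groups, so the target has no margin and the correct 124 cannot be placed in 15 groups of at most eight.

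Severity is minor. If 0.70 is Cohen's d, the arms are equal and the test is a single unadjusted two-sided pairwise comparison, power after the stated loss is about 81% with full groups and about 68% with every group at six. Both figures are before clustering and do not describe the planned longitudinal model. Nothing here shows that 105 was wrongly derived or that the stated 80% is lost when groups are full.

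**What to change.** Keep 120 and restate the figures in section 2.3, for example:

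> 120 participants will be randomised (8 in each of 15 groups). With 15% loss, 102 remain (34 per arm), giving about 81% power for one two-sided pairwise comparison at d = 0.70, before clustering. If all groups run at 6 (90 enrolled, about 25 per arm retained), this power falls to about 68%.

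This replaces 105 with the number actually expected and makes the dependence on full groups visible. If 105 is to stay as the requirement, the target must become 124, and the number or size of groups must change to hold it.

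The first option costs only a change of wording, with no extra recruitment and no change of design. The stated position becomes slightly less favourable, because the margin above 80% is thin and depends on every group being full.

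The six-month phrase, the label on the effect size and the comparison of SD-PLUS with SD need no change on this account.

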### 2.6. Randomization

A computerized random number generator in Microsoft Excel is used to allocate participants into the different arms of the study. A research assistant from the research team will undertake the randomization, and the randomization results will be provided to the social workers of the participating NGOs. They are then responsible for contacting the participants, securing their consent and informing them of the session schedule.

Pre-group interviews will be conducted after the randomization. The objective of the pre-group interview is to enhance participants’ understanding of the study’s objectives and the schedule of the intervention groups, and to help group facilitators to familiarize themselves with the learning characteristics and group experience of the individual participants.

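### The 105 participants for 80% power assume independent individuals, although all three arms are delivered in 15 small groups

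*Protocol article*

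**What the plan says.** Section 2.3 of the protocol article states the calculation: "The sample size is calculated based on a moderate effect size of 0.70 for clinical outcome research", and then "For 80% power, an α error of 0.05, and a test including three independent groups, the required sample size is 105 participants". Drop-out is the only inflation: "Incorporating an estimated drop-out rate of 15% at the six-month follow-up period, the target sample size is 120". The section closes by fixing how the arms are run: "With 6–8 participants per group, 5 SD groups, 5 SD-PLUS groups and 5 leisure groups will be conducted". So there are 15 delivery groups, and the leisure arm is grouped as well. Allocation is of individuals (section 2.6).

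Section 1.1 justifies the group format by, among other things, "individual change caused by group dynamics and interpersonal change processes".

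Section 2.12 names HLM with a time by treatment interaction. It supports the choice by the handling of missing data and by saying that the method "stresses individual change over group differences". It does not list levels or random effects.

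**The concern.** Members of one group share a facilitator, a co-worker and peers for ten sessions. The protocol expects that shared experience to produce change, so outcomes at T1 and T2 should be correlated within groups. Positive correlation means that 35 people in five groups carry less information about an arm than 35 unrelated people. A power figure that ignores this is too high.

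The same correlation matters for the test. A model without therapy group would give standard errors that are too small on the primary outcome. Section 2.9.3 also makes the later offer to the leisure arm depend on significant enhancement on the primary outcome, so a false positive or a missed effect has a practical consequence.

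**Working it through.** **Inputs.** From section 2.3: standardised difference d = 0.70, alpha 0.05, power 80%, three arms, 105 evaluable, 120 enrolled, 5 groups per arm. Two-sided testing is assumed, because the section does not state sidedness. Evaluable group size is m = 105/15 = 7 (35 per arm); with everyone retained, m = 120/15 = 8 (40 per arm). The ICC is not in the document, so 0.01 to 0.10 is assumed.

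**Step 1: reproduce 105.** A two-sided two-sample t-test with d = 0.70 and 80% power (noncentral t) needs 33.02, so 34 per arm and 3 × 34 = 102, within 3% of 105. Alternatives fit less well:
- normal approximation: 99
- one-sided test: 78
- three-arm one-way ANOVA with a largest difference of 0.70: about 92 or 121, depending on the pattern of means
- Bonferroni for two or three contrasts: 123 or 135

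The best match therefore has a design effect of 1. At 35 per arm this test has 82% power.

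**Step 2: allow for the groups.** DE = 1 + (m − 1) × ICC. The noncentrality is 0.70 / √(2 × DE / n), with n per arm. For example, at m = 7 and ICC 0.05, DE = 1 + 6 × 0.05 = 1.30 and the noncentrality is 0.70 / √(2 × 1.30 / 35) = 2.57. Power is given first with the degrees of freedom of an individual-level t-test (2n − 2), then with 12 (15 groups minus 3 arms).

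| Evaluable per group | ICC | DE | Power, 2n − 2 df | Power, 12 df |
|---|---|---|---|---|
| 7 | 0.01 | 1.06 | 80% | 74% |
| 7 | 0.05 | 1.30 | 72% | 66% |
| 7 | 0.10 | 1.60 | 63% | 57% |
| 8 | 0.01 | 1.07 | 85% | 79% |
| 8 | 0.05 | 1.35 | 76% | 70% |
| 8 | 0.10 | 1.70 | 66% | 60% |

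By the design effect alone, 105 independent participants correspond to 105 × 1.06 = 112, 105 × 1.30 = 137 and 105 × 1.60 = 168 evaluable (rounded up).

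**Step 3: baseline adjustment.** Groups form after baseline, so adjustment is taken to reduce the individual variance and to leave the group component as it is. DE is replaced by (1 − r²) + (m − 1) × ICC. With an assumed baseline correlation r = 0.6 and m = 7, this is 0.70, 0.94 and 1.24 at ICC 0.01, 0.05 and 0.10. Power is then 93%, 85% and 74%, or 89%, 79% and 68% with 12 df.

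**Step 4: type I error if therapy group were left out of the model.** This is 2 × (1 − Φ(1.96 / √DE)). At ICC 0.01, 0.05 and 0.10 it is 5.7%, 8.6% and 12.1% for m = 7, and 5.8%, 9.2% and 13.3% for m = 8. A simulation of a two-arm t-test (40,000 runs) gave 5.7%, 8.3% and 12.7%, and 5.8%, 9.3% and 13.3%.

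**The case against.** A reader might infer from section 2.12 that the HLM treats participants as independent and that the p-values will be too small. The document does not show that. It states no levels, so it neither includes nor excludes therapy group; an HLM can carry that level, and a condensed article may leave the structure to a fuller document. The remark about individual change describes HLM in general and is no evidence of an omission. This part of the objection stands, so the type I figures are conditional.

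A reader might also take the maximum likelihood sentence in section 2.12 as a faulty choice for estimating a between-group variance from 15 groups. That sentence is about participants who withdraw and does not say how variance components are fitted, so it is no error. The phrase about three independent groups in section 2.3 refers to the arms. It is the arithmetic, not that phrase, that shows independence was assumed.

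On size, the ICC is assumed. At 0.01 without a degrees-of-freedom correction, 80% is still reached. Treating each pair of arms as its own 10-group analysis with 8 df would be the pessimistic end (70%, 62% and 53% at m = 7); a single three-arm model has 12. Removing every drop-out is also severe under intention to treat, and the planned model uses baseline data. These points limit the loss. They do not supply the missing allowance, because section 2.3 states its calculation and its only inflation.

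**Conclusion.** The point holds for the sample size. The stated 80% power is for independent individuals, and the design fixed in the same section does not support it over most of the assumed ICC range. Without baseline adjustment, power runs from about 80% down to 63% with 7 evaluable per group (74% to 57% with 12 df), and from 85% down to 66% with all 120 retained (79% to 60% with 12 df). A shortfall is likely rather than certain. It vanishes at a very small ICC if degrees of freedom are not corrected, and a strong baseline correlation would offset part or all of it.

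For the analysis, the conclusion is conditional: if therapy group is not a level of the HLM, the nominal 5% test would have a true error of about 6% to 12–13% over the same range. The document does not settle whether it is a level.

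**What to change.** Keep N at 120. In section 2.3, replace the 80% power statement with the power at 15 groups over a stated ICC range such as 0.01 to 0.10, showing any baseline correlation relied on. In section 2.12, state that participants are nested in therapy group and that the HLM has a random effect for it in all three arms, with small-sample degrees of freedom (for example REML with Kenward-Roger or Satterthwaite).

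This changes wording and model specification only. It needs no extra participants and no change to the allocation procedure. The cost is wider confidence intervals and a less favourable stated power.
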